# Effects of three home-based exercise programmes regarding falls, quality of life and exercise-adherence in older adults at risk of falling: protocol for a randomized controlled trial

**DOI:** 10.1186/s12877-018-1021-y

**Published:** 2019-01-14

**Keywords:** Older adults, Home-based exercises programmes, Falls, Quality of life, Exercise-adherence

## Abstract

**Background:**

Fall prevention interventions with home-based exercise programmes are effective to reduce the number and the rate of falls, by reducing risk factors. They improve balance, strength, function, physical activity, but it is known that older adults’ exercise adherence declines over time. However, it is unclear which delivery-modalities of the home-based exercise programmes show the best adherence and the largest effect.

We created a new home-based exercise programme, the Test-and-Exercise (T&E) programme, based on the concepts of self-efficacy and empowerment. Patients learn to build their own exercise programme with a mobile application, a brochure and cards, as well as with eight coaching sessions by physiotherapists.

The main objective of this study is to compare the T&E programme with the Otago Exercise Programme and the recommendation-booklet and exercise-cards of Helsana regarding incidence of falls. Other outcomes are severity of falls, functional capacities, quality of life and exercise-adherence.

**Methods:**

The design of this study is a Swiss multicentre assessor blind randomized controlled trial. A block-randomization, stratified in groups for age and risk of fall categories, will be used to allocate the participants to three groups. The targeted study sample consists of 405 older adults, ≥ 65 years of age, living in the community and evaluated as at “risk of falling”. Experimental group will receive the T&E programme (*N* = 162). Second group will receive the Otago programme (*N* = 162) and the third group will receive the Helsana programme (*N* = 81). All interventions last six months. Blinded assessors will assess participants three times: at baseline before the start of the intervention, after six months of intervention and a final assessment after twelve months (six months of follow up).

**Discussion:**

Although home-based exercises programmes show positive effects in fall prevention in elderly persons, existing programmes do often not include patients in the decision-making process about exercise selection. In our programme the physiotherapist and the older adult work together to select the exercises; this collaboration helps to increase health literacy, pleasure of exercising, and empowers patients to be more autonomy.

**Trial registration:**

ClinicalTrials.gov: NCT02926105, First Posted: October 6, 2016, Last Update: November 11, 2016: Enrolment of the first participant.

## Background

Falls are one of the major health problems affecting the quality of life in older adults [1, 2] and are particularly common and burdensome in the elderly population [3]. Of community-dwelling older adults over 64 years of age, 28–35% fall each year and the frequency of falls increases with age and frailty level [4], up to 50% in the elderly aged more than 80 years [5]. It represents a serious public health problem due to high healthcare demands and related healthcare costs and has a major impact on the individual patient [6].

Consequences of these falls are somatic, psychological, social and economic [7, 8]. They induce loss of confidence and fear of further falls [9], chronic pain, loss of independence and reduced quality of life [10] as well as economic cost greater than policy makers appreciate [11]. In 10 to 20% of the cases, falls result in bone fractures and head injuries [12] and can lead to increased mortality [7, 12]. It may not be possible to prevent falls completely, but people who tend to fall frequently may be enabled to fall less often [13].

However, for the older adults, living in their own home or in institution, physical and psychological impairment and functional limitations worsen significantly the quality of life [14]. Thus, in older adults at risk to fall, balance, functional mobility, muscle strength and fear of falling are associated with quality of life [15–21].

Regular physical activity could be a way to slow down the decline and maintain or even increase personal autonomy and quality of life [22]. According to the recommendations and strategies for promoting exercise in older adults [23], elderly people at risk could also profit from adapted exercise programmes [24–26]. Fall prevention interventions that include exercise programmes are recognized as effective to reduce the incidence of falls in elderly community-dwelling individuals [13, 27–29], seem to prevent injuries caused by falls [30] and show significant improvement in quality of life in frail older adults [31], as well as in women with osteopenia or osteoporosis [32]. However, the question about optimal methods for exercise delivery, exercise selection and exercise progression is not yet conclusively answered.

Home-based exercise programmes appear to reduce rate of falls [33], number of fallers, risk factors for falls, and risk of death [34] by improving balance, leg strength, function, physical activity [35] and balance confidence in older adults living in the community [36].

To maintain the effects of the home-based exercise programmes, older people should continue as long as possible with these exercises. However, older adult’s adherence to exercise interventions declines over time [37, 38]. A variety of factors determine, increase or decrease adherence to exercise in older adults [39]. These factors could be psychological and cognitive, behavioural, physical or simply organisational. The strongest motivator affecting exercise adherence in older adults is *self-efficacy* [39] and the integration of the *self-efficacy* concept in exercise programmes to enable individuals to continue with the programme is highly recommended [37, 40].

Because *self-efficacy* is a modifiable factor, project promoters and researchers could enhance the adherence in falls-prevention interventions using specific recommendations [41]. There also is a range of factors affecting the implementation of fall-prevention practices. They are related to older adults, families, healthcare professionals and healthcare systems [42]. General considerations consist in raising awareness in the population and in health professionals [7, 43], promotion of benefits of exercises in older people [43, 44] and consideration of the individual lifestyle, values and capabilities [7, 43, 44]. More specific, encouraging confidence in self-management by giving older adults an active role [43] and providing moderate follow-up visits [7, 45] could improve adherence to home exercise programmes for prevention of falls. Currently, with the advent of e-technology, several studies use mobile applications [46–49] to improve adherence and motivate older adults living in their own home to exercise. Therefore, we developed a new home-based exercise programme, based on the concepts of self-efficacy and of empowerment, delivered on a mobile application. Because older people have to test the exercises before starting to train, this programme is named Test and Exercise (T&E).

The aim of this study is to compare the effects of the T&E exercise programme with the effects of the Otago and Helsana exercise programmes in older adults at-risk for falling, while living in their own home.

Our hypothesis is that the reference intervention (Otago) is superior to the usual care (Helsana) and that the experimental intervention (T&E) is non-inferior to the reference intervention.

## Methods/design

### Study design

The study design is a multicentre randomized controlled trial, assessor blinded, with three groups. It follows the recommendations of SPIRIT 2013 [50]. The trial is executed at the homes of the participants in four Swiss regions: Zurich, Vaud, Bas-Valais and Haut-Valais.

### Participants

The population consists of older adults > 65 years, living in their own home and identified as at-risk of falling. Table 1 shows the inclusion and exclusion criteria.

**Table 1 Tab1:** Inclusion and exclusion criteria

Inclusion criteria	Exclusion criteria
Older adults aged ≥ 65 years living independently at home	Severe vision impairments that do not permit the reading of the exercise-programme booklet and that do not permit the completing of the monthly diaries
Able to walk without mobility aids in their home	In physiotherapy treatment that trains balance
History of fall in the previous 12 months or perceiving fear of falling (≥ 20 points [98] on FES-I [63])	Cognitive impairment (< 24 points [99] on the Minimal Mental State Examination [100])
Good understanding of the Trial language (French or German)	Contraindication given by the referring physician

### Recruitment, randomization, blinding and treatment allocation

Caregivers (medical doctors, nurses, physiotherapists) in partner hospitals, health-care centres and medical offices will recruit the participants. To achieve adequate enrolment to reach target sample size, we projected to enrol a quarter of the sample size in each region (101/region) for three years (from August 2016 to September 2019). In addition, the local coordinators will meet the recruitment partners twice a year. They will give a feed-back about the progress state on the trial and motivate them to continue the recruitment.

The local coordinators will verify the eligibility criteria (Table 1) at the home of the participants.

The final decision on inclusion or exclusion and randomization takes place after the baseline assessment. A researcher who is not involved in the study creates an allocation list with a computer generated random sequence using the command “ralloc” within Stata (StataCorp, college Station, Texas, USA), version 14.2. A block-randomization is executed stratified in groups of age (65–79; > 80 years old) and in risk of fall categories [51] (low-moderate; high). If a couple living in the same house will participate, both persons will be randomized in the same intervention group [52].

The randomization was integrated in the software for Research Electronic Data Capture (REDCap [53]) and is concealed to all members of the research team. The project assistant manually triggers the randomization after the baseline assessment. The local coordinators will take note of the allocation group in REDCap.

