### Outcomes

The primary outcome “falls incidence” and exercise frequency will be assessed prospectively and for twelve months with self-recorded monthly diaries. If a patient decides to stop his participation (completing monthly diaries and exercise training), the physiotherapist will ask him to participate at the intermediary or/and finale assessment. Physiotherapist-assessors who are unaware of group allocation (“blinded assessors”) will assess the secondary outcomes at baseline, at the six-month intermediary assessment, and at the twelve-month final assessment. All assessors are independent physiotherapists and specially trained to perform the assessments.

To ensure that the assessors remain unaware of the group allocation, patients are told not to talk about their treatment with the assessor.

The main outcome is the incidence of falls for twelve months. For this study we define a fall as “*an unexpected event in which the participant comes to rest on the ground, floor, or lower level, with or without injury*” as recommended in the systematic review of Hauer et al. [59]. The history of falls (number, circumstance (Where? *Inside OR outside;* When? *Day OR night;* How? *Describe shortly the event*) and severity) in the previous twelve months will be assessed at baseline. During the study, falls will be prospectively self-reported (number, date, circumstance and severity) in monthly diaries [60]. To ensure that the patients complete the diaries, the physiotherapists will check them at each visit and ask about the diaries during each phone call [59]. In addition, falls events (number, circumstance and severity) will be asked during the intermediary assessment and at the final assessment. The diaries will be sent to the coordinators. The coordinators will send them in PDF version to the project-assistant. She will enter the data in REDCap software once a month.

Secondary outcomes include severity of falls, fear of falling, gait, strength and balance and quality of life. They will be assessed at baseline, at the intermediary assessment and at the final assessment. They also include exercise-adherence. This outcome will be assessed at twelve months.

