### Sample size

To achieve our study objectives, the sample size calculation estimates 405 participants. With a significance level set at 5% (i.e. overall type-I error probability) and power of 80%, an assumed rate of falls of 0.5 for the T&E program, 0.79 for the OTAGO and 0.92 for the usual care group, a non-inferiority margin of 5% and an assumed dropout rate of 15%, we would need to include 162 participants in the groups A and B each, and 81 participants in the group C. We used the R package “ThreeArmedTrials” to calculate the sample size [83].

The allocation scheme of 2:2:1 is based on ethical and statistical considerations, following the recommendations of Mütze et al. [84] and Mielke et al. [85].

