### Statistical analysis

Descriptive statistics will be used to present group characteristics on age, sex, body mass index, base of support width (BSW) [86, 87], and history of falls, activity of daily live, physical activity habits, and risk factors for falls.

According to statistical criteria of termination of the trial, we have no predefined stopping rules because we are not expecting risks that are different in the groups (i.e. no adverse event stopping criteria).

We will use an intention-to-treat analysis based on all randomized patients, with missing values and dropouts replaced by multiple imputation methods, as recommended by current guidelines on randomized controlled trials [88].

The primary analysis will be done to test for the incidence of falls. We follow the proposition of Röhmel and Pigeot [89], who showed that superiority of the experimental group (“T&E” in our case) over the reference treatment (“Otago” in our case) can be tested after successfully demonstrating non-inferiority (if stated a-priori in the protocol). To simultaneously demonstrate superiority of E (T&E) to R (Otago) and R (Otago) to P(Helsana) as well as the non-inferiority of E (T&E) to R (Otago), we will use negative binomial regression [90, 91] and follow an approach proposed by Mütze et al. [84]. A sensitivity analysis without multiple imputations of missing values will be performed.

For the primary analyses, we will adjust for the participants’ length of observation, center, age and risk for falls category [92]. We will perform a per protocol sensitivity analysis including time varying co-variables to reduce confounding and selection bias, e.g. due to differential censoring.

Further analyses will be performed to test the secondary endpoints quality of life (Overall score of OPQOL-35), severity of falls (Schwenk Scale), fear of falling (FES-I), functional capacities (TUG, FSBT, FTSTS, FR and SMWT), as well as adherence to the exercise recommendations (duration in min/week, frequencies/week).

We will perform a subgroup analysis based on age groups to test the secondary hypothesis that compliance in older group is better with the Otago compared to T&E and that in younger participants’ compliance is better in T&E compared to Otago.

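### Couples are randomised together, but the stated primary model names no household term or clustered variance; if partners' outcomes correlate positively, standard errors are slightly too small

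*Protocol article*

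**What the plan says.** Under the heading on recruitment, randomisation, blinding and allocation, the protocol article describes block randomisation stratified by age group and fall-risk category, triggered after the baseline assessment. It then adds a rule for couples: "If a couple living in the same house will participate, both persons will be randomized in the same intervention group".

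Under Outcomes: "The main outcome is the incidence of falls for twelve months", recorded in monthly diaries. Exercise adherence, also taken from diaries, is a secondary outcome.

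Under Statistical analysis, for the three-arm comparison: "we will use negative binomial regression". The adjustment set for the primary analyses is "length of observation, center, age and risk for falls category". Missing values are multiply imputed.

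Under Sample size, 405 participants are planned (162, 162 and 81) at 5% overall type I error, 80% power and 15% dropout. No allowance for paired allocation is mentioned there. No section gives an expected number of couples.

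**The concern.** The allocation rule creates clusters of two. Partners share a home, and the programmes are delivered and practised in the home, so their fall counts, and even more their exercise habits, may be correlated. Both partners are in the same arm by design, so a positive correlation adds to the variance of that arm's estimated rate and does not cancel between arms.

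Nothing in the stated model picks this up. The negative binomial dispersion parameter describes extra variation between individuals, not covariance between two particular people. Centre, age and fall-risk category may absorb some of the shared risk, but not what is specific to one household.

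At stake is the nominal accuracy of the confidence intervals, including the one that decides non-inferiority of T&E to Otago, and of the adherence comparisons, where the authors expect T&E to do better.

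**Working it through.** **Inputs from the article.** N = 405 (162 + 162 + 81); two-sided 5% taken for illustration, because sidedness is not stated; power 80%; dropout 15%; assumed fall rates 0.5, 0.79 and 0.92.

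**Inputs that must be assumed.** f, the share of participants enrolled as one of a couple, and ICC, the within-couple correlation of the outcome. Neither is in the article. I take f = 10–20%, which is about 40 to 81 people or 20 to 40 couples out of 405. I take ICC = 0.1–0.3 for falls and 0.5 as an illustration for adherence.

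**Step 1. The plan's own figure.** 162 + 162 + 81 = 405 fits 2:2:1. 405 × 0.85 = 344.25, and 344 / 0.85 = 404.7, which rounds up to 405, so the dropout inflation is coherent. The base of about 344 cannot be reproduced uniquely, because the article does not give the dispersion, the sidedness or the scale of the 5% margin. Wald-type negative binomial formulas for T&E against Otago reach it only by choosing the dispersion: about 0.20 to 0.94 at one-sided 0.025 and about 0.70 to 1.60 at one-sided 0.05, depending on how the margin is read. The shifts below are therefore measured against the nominal 5% and 80%.

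**Step 2. Design effect.** Take n people in one arm, each with outcome variance s². A fraction f of them are in pairs, which makes n·f/2 pairs.

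Var(sum) = n·s² + 2·(n·f/2)·ICC·s² = n·s²·(1 + f·ICC)

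So DEFF = 1 + f·ICC, and the correct standard error is √DEFF times the naive one. Actual two-sided type I error = 2·[1 − Φ(1.96/√DEFF)]. Power = Φ((1.96 + 0.842)/√DEFF − 1.96).

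**Step 3. Numbers for falls.**

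| f | ICC | DEFF | SE too small by | Actual type I error | Power | N to compensate |
|---|---|---|---|---|---|---|
| 10% | 0.1 | 1.01 | 0.5% | 5.1% | 79.6% | 410 |
| 10% | 0.3 | 1.03 | 1.5% | 5.4% | 78.8% | 418 |
| 20% | 0.2 | 1.04 | 2.0% | 5.5% | 78.4% | 422 |
| 20% | 0.3 | 1.06 | 3.0% | 5.7% | 77.7% | 430 |

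The type I error column applies to an analysis that ignores the pairing. The power column applies to one that allows for it.

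**Step 4. A wider range.** With f = 5–30% and ICC = 0.01–0.3, DEFF runs from 1.0005 to 1.09, the SE shortfall from 0.02% to 4.4%, and actual type I error from 5.01% to 6.05%.

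**Step 5. Adherence, ICC 0.5 assumed.** f = 10%: DEFF 1.05, √1.05 = 1.025, type I error about 5.6%. f = 20%: DEFF 1.10, √1.10 = 1.049, type I error about 6.2%.

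**The case against.** A reader might infer that the plan treats all participants as independent. The article does not say so. It names a model family and a list of covariates. A cluster-robust variance is not a covariate and would not appear in that list, and the choice of variance estimator is the kind of detail that a condensed article leaves to an analysis plan. That stands: the point can only be that the stated model does not carry through the stated allocation rule.

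A reader might also infer that the intervals and the non-inferiority decision are anti-conservative. That holds only if the correlation is positive. A negative one would make the naive standard errors too large. The effect is also bounded, because clusters have at most two members and only couples are affected. For fall counts the correlation has a ceiling of φμ/(1 + φμ). With an assumed dispersion φ = 1 and the article's rates of 0.5 and 0.79, that ceiling is 0.5/1.5 = 0.33 and 0.79/1.79 = 0.44, reached only if partners had identical underlying risk. An ICC of 0.3 is thus towards the upper end. This stands too, and it keeps the point small.

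A third tempting inference is that allocation concealment is lost for a partner who joins later. If one partner were enrolled after the other had been allocated, the second arm would indeed be known in advance. But no section describes staggered enrolment of partners, and the article places randomisation after the baseline assessment, concealed from the research team. Joint randomisation after both baselines is compatible with the text and may already be the practice. The risk is conditional.

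What the objection does not remove is that the couples rule was foreseen and written down, while no matching provision appears in the model or the sample size.

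**Conclusion.** The point holds in modest form. Joint allocation of couples is stated, and the stated primary model names nothing to account for it. Under an assumed 10–20% of participants in couples and an assumed positive ICC of 0.1–0.3 for falls, the design effect is 1.01–1.06 and the standard error is understated by about 0.5–3%. Adherence could be affected more, about 2.5–5% at an assumed ICC of 0.5. Joint allocation itself is not an error. An effect of this size is unlikely to change a clear result, although it could matter for an interval that ends close to the non-inferiority margin. It is worth acting on because the mismatch comes from the trial's own allocation rule and is nearly free to correct.

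**What to change.** - Record a household ID for every participant; people enrolled alone form clusters of one.
- State that the primary and secondary models use household-clustered robust standard errors, computed within each imputed dataset before pooling. With 10–20% in couples there would be about 365 to 385 households overall and about 73 to 77 in the Helsana arm, which is ample for a robust variance. A household random intercept is an alternative, but with mostly single-person households it is hard to separate from the negative binomial dispersion.
- Report the number of couples in each arm.
- Where both partners are known to be joining, randomise the couple once, after both baseline assessments. This closes the conditional concealment risk.
- A sensitivity analysis that keeps only the first-enrolled partner is optional.

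The cost is one variable, one model option and slightly wider intervals. On the falls assumptions above, full compensation would take 5 to 25 more participants (410 to 430 in place of 405), but accepting the small loss of power is reasonable.

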### Informed consent

All eligible patients are informed about this study and given the time they need to consider participation. The investigators and the local coordinators may be approached for questions. Patients who accept to participate will sign an informed consent form and transmit it to the local coordinator.

